# Introduction

Tuberculous meningitis is the severest form of infection with *Mycobacterium tuberculosis,*

causing death or severe neurologic deficits in more than half of those affected in spite of antituberculosis chemotherapy [1, 2]. Early studies suggested that corticosteroids reduced cerebrospinal fluid inflammation and time to recovery in patients with tuberculous meningitis, but the studies were too small to confirm any effect on survival [3-7]. Concern remained that corticosteroids might reduce the case fatality rate but increase the number of disabled patients [8]. Randomized trials performed in Egypt [9] and South Africa [10] provided evidence that corticosteroids improved survival in children with severe disease and probably reduced neurologic sequelae. A meta-analysis of all randomized controlled trials of corticosteroids for tuberculous meningitis suggested that corticosteroids were effective in reducing the risk of death in children but not in patients over 14 years of age although only six trials involving a total of 595 patients (158 adults) met the inclusion criteria, and there were no data on human immunodeficiency virus (HIV) co-infected patients [11]. The authors concluded that small numbers of patients, poor concealment of the treatment-group assignments, and publication bias could account for the positive results, and that studies in patients with HIV infection and studies of a size large enough to assess morbidity and the case fatality rate were required. We therefore conducted a randomized, double-blind, placebo-controlled trial to determine whether adjunctive dexamethasone therapy reduced the risk of death or disability in Vietnamese adults (15 years old).

The results of the study were as follows. A total of 545 patients were randomly assigned to groups that received either dexamethasone (274 patients) or placebo (271 patients). Only 10 patients (1.8 percent) had been lost to follow-up at nine months of treatment. Treatment with dexamethasone was associated with a reduced risk of death (relative risk, 0.69; 95 percent confidence interval, 0.52 to 0.92; P=0.01). It was not associated with a significant reduction in the

proportion of severely disabled patients (34 of 187 patients [18.2 percent] among survivors in the dexamethasone group vs. 22 of 159 patients [13.8 percent] in the placebo group, P=0.27) or in the proportion of patients who had either died or were severely disabled after nine months (odds ratio, 0.81; 95 percent confidence interval, 0.58 to 1.13; P=0.22). The treatment effect was consistent across subgroups that were defined by disease-severity grade (stratified relative risk of death, 0.68; 95 percent confidence interval, 0.52 to 0.91; P=0.007) and by HIV status (stratified relative risk of death, 0.78; 95 percent confidence interval, 0.59 to 1.04; P=0.08). Significantly fewer serious adverse events occurred in the dexamethasone group than in the placebo group (26 of 274 patients vs. 45 of 271 patients, P=0.02). We therefore concluded that adjunctive treatment with dexamethasone improved survival in Vietnamese patients over 14 years of age with tuberculous meningitis but probably did not prevent severe disability[12].

One of the limitations of previous studies of patients with tuberculous meningitis is the duration of follow-up after the end of tuberculosis treatment. There are scanty data available about relapse rates and no information about long term outcome. Although the dexamethasone study showed a reduction in mortality we do not know if this benefit persists and, if so, for how long. We also do not know the outcome of patients who were severely disabled at the end of treatment. We therefore propose to conduct a simple study to determine the long-term outcome in patients recruited to the dexamethasone study 5 years after recruitment into the original study.

The questions that we seek to answer are:

1. Does the difference in mortality between the 2 groups persist at 5 years?
2. Are there differences in neurological disability between the 2 groups at 5 years?
3. Are there differences in TB relapse rates between the 2 groups?

## Methods

The study will be conducted at the Hospital for Tropical Diseases (HTD) and Pham Ngoc Thach Hospital (PNT) in Ho Chi Minh City, Vietnam

All patients who were alive at the end of the dexamethasone study (n=340) will be eligible to participate in this long-term follow-up study.

Patients will be sent an invitation letter (Appendix 1) containing a simple questionnaire to complete and return. Those that do not return the questionnaire will be contacted by telephone or traced through the local health services.

Written informed consent (Appendix 2) will be obtained from all patients or their relatives (if the patient is unable to give consent).

Those patients who agree to participate and are able to travel to the hospital will be offered an appointment and their transport costs will be reimbursed.

Those patients who agree to participate in the study, but who are unable to travel to hospital to attend an appointment, will be assessed at home by a doctor.

The assessment will consist of a simple questionnaire, a clinical examination and a blood test.

Data will be collected in individual case record forms and entered into a computer database.

The study will be co-ordinated by [name] (Oxford University Clinical Research Unit), [name] [name] (Hospital for Tropical Diseases) and [name] [name] (Pham Ngoc Thach Hospital)

## Outcome measures

The outcome measures for the study are:

1. Survival at 5 years
2. Neurological disability at 5 years
3. TB relapse rate

## Statistical analysis

This will be performed by [name] using STATA. The following analyses will be performed:

1. Kaplan-Meier survival estimates and log rank test
2. Comparison of disability scores between 2 groups by chi square test
3. Comparison of TB relapse rate between 2 groups by chi square test

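### The planned 5-year disability comparison can take in only survivors, and the plan lists no outcome that counts death together with disability

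*Protocol*

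**What the plan says.** The second of the three study questions in the protocol's Introduction is "Are there differences in neurological disability between the 2 groups at 5 years". Under Outcome measures, neurological disability at 5 years is listed separately from survival, and nothing on the list combines the two. Under Statistical analysis, the matching entry is "Comparison of disability scores between 2 groups by chi square test". It gives no analysis population and no rule for patients who have died.

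Methods limits eligibility to the 340 patients alive when the dexamethasone study ended. Information is gathered by questionnaire, examination and blood test.

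The Introduction reports the parent trial in three relevant pieces:
- Mortality: dexamethasone was associated with a "reduced risk of death (relative risk, 0.69; 95 percent confidence interval, 0.52 to 0.92; P=0.01".
- Disability among survivors: "34 of 187 patients [18.2 percent] among survivors in the dexamethasone group" against "22 of 159 patients [13.8 percent] in the placebo group, P=0.27".
- The combined outcome, for patients who had "died or were severely disabled after nine months (odds ratio, 0.81; 95 percent confidence interval, 0.58 to 1.13; P=0.22".

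The parent trial therefore set a death-inclusive result beside the survivor result. The follow-up plan carries forward only a disability comparison.

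**The concern.** A disability score is available only for someone alive to be assessed. If treatment affects who is alive, the two sets of scored patients are no longer the groups that randomisation made comparable. Should the patients kept alive by dexamethasone be more disabled on average than other survivors, the dexamethasone survivors will look worse even if no patient was harmed.

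This bears directly on the study's purpose. The Introduction raises the old worry that corticosteroids might lower case fatality at the price of more disabled patients. A comparison of survivors alone cannot separate that trade-off from harm to patients who would have lived anyway. Without a death-inclusive result beside it, a higher disability rate on dexamethasone at 5 years could be read as a drug effect on disability.

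**Working it through.** **Inputs (all from the Introduction).** Randomised: "dexamethasone (274 patients) or placebo (271 patients". Severe disability among survivors: 34/187 and 22/159. Losses: "Only 10 patients (1.8 percent) had been lost to follow-up at nine months of treatment", with no split by arm.

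**1. Reproduce the survivor result.** 34/187 = 18.2% and 22/159 = 13.8%. Pearson chi-square without continuity correction gives P=0.27, as stated.
- OR = (34/153)/(22/137) = 1.38.
- SE of log OR = √(1/34 + 1/153 + 1/22 + 1/137) = 0.298; 95% CI 0.77 to 2.48.
- Risk difference +4.3 points (95% CI −3.4 to +12.1).

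**2. Reproduce the combined result.** Count everyone outside the survivor denominators as dead.
- Dexamethasone: 274 − 187 = 87; 87 + 34 = 121; 121/274 = 44.2%.
- Placebo: 271 − 159 = 112; 112 + 22 = 134; 134/271 = 49.4%.
- OR = (121/153)/(134/137) = 0.81.
- SE of log OR = √(1/121 + 1/153 + 1/134 + 1/137) = 0.172; 95% CI 0.58 to 1.13, P=0.22. This matches the stated figure.
- Risk difference −5.3 points (95% CI −13.7 to +3.1).

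**3. Selection into the scored set.** 187/274 = 68.2% against 159/271 = 58.7%, P=0.02. Membership of the survivor denominators differs by arm.

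**4. What moves the estimate across 1.** Severe disability alone over all randomised patients is 34/274 = 12.4% against 22/271 = 8.1% (OR 1.60, 95% CI 0.91 to 2.82, P=0.10). This still points against dexamethasone, because a patient who dies early cannot be counted as disabled. The estimate crosses 1 only when death enters the outcome.

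**5. Sensitivity to the 10 losses.** Assume that all 10 lie among the 87 + 112 = 199 patients outside the survivor denominators, and try every split by arm.
- Losses counted as non-events: from (111/163)/(134/137) = 0.70 (all in dexamethasone) to (121/153)/(124/147) = 0.94 (all in placebo).
- Losses excluded: from (111/153)/(134/137) = 0.74 to (121/153)/(124/137) = 0.87.

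The combined OR stays below 1 throughout.

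**6. Illustration of the mechanism.** Placebo rates applied to 274 patients give 159/271 × 274 = 160.8 survivors and 22/271 × 274 = 22.2 severely disabled. The dexamethasone arm had 187 − 160.8 = 26.2 more survivors and 34 − 22.2 = 11.8 more severely disabled. If the treatment saved those extra survivors, and about 11.8/26.2 = 45% of them were severely disabled, the whole survivor difference would arise with nobody made worse. The data do not show that this happened; they are compatible with it.

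**7. An unordered alternative.** A chi-square on three unordered categories (alive without severe disability, severely disabled, dead: 153/34/87 against 137/22/112) gives P=0.037 but no direction.

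**The case against.** The strongest reply is that the protocol never says the comparison is confined to survivors. Methods settles who is invited and examined, not who enters the analysis. A disability score with death as its worst level could be tested by chi-square without contradicting the text, and a statistical analysis plan that is not shown may say so. This stands in part: the restriction is an inference. It is still the natural reading, because disability and survival are separate outcomes, the listed analyses contain no combined one, and the Introduction's own disability figures use survivor denominators.

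A second reply is that the 9-month contrast sets different endpoints side by side. Of the combined events, 87 of 121 and 112 of 134 lie outside the survivor denominators, so the favourable estimate largely restates the mortality benefit. That is right. The contrast is not a measure of bias in the disability estimate.

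A third reply is that a composite treats death and severe disability as equal and can hide the trade-off that the Introduction worries about. It is also legitimate to ask how survivors fare, including those severely disabled at the end of treatment. Both points stand. They argue for showing the components and keeping the survivor description, not for omitting a death-inclusive result.

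A reader might infer that the result reverses once all randomised patients form the denominator. Step 4 of the working shows that it does not. A reader might also infer two established and conflicting effects; both intervals include 1 and they overlap. Nor is the chi-square test itself at fault, since a binary combined outcome could use it.

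**Conclusion.** The point holds as a change the sponsor should make. Followed as written, the plan would answer its second question with a comparison that is most naturally read as selected by survival, an event that treatment affected, and it drops the parent trial's companion outcome.

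The protocol's own 9-month figures show how much the choice can matter: OR 1.38 among survivors against OR 0.81 for death or severe disability in all randomised patients. Both are non-significant.

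The conclusion rests on the survivor restriction, which is inferred, and on counting patients outside the survivor denominators as dead. The side of 1 on which the combined estimate falls does not depend on how the 10 losses are split. The survivor denominators sum to 187 + 159 = 346, while Methods gives 340 eligible; the documents do not explain the gap, and the point does not depend on it. Deaths between 9 months and 5 years could change the selection further, but the documents give no figure for its size. The survival comparison, listed first with its own log-rank test, is not touched by this.

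**What to change.** In Outcome measures item 2 and Statistical analysis item 2:
- Add death or severe disability at 5 years, by randomised arm, in all 545 patients, with an odds ratio or risk difference and its 95% CI. Alternatively, use an ordered disability scale with death as the worst category and a method that respects the order. An unordered chi-square would not give a direction.
- Show deaths and severe disability separately by arm beside the combined result.
- State how patients lost by 9 months, and patients untraced at 5 years, are handled.
- Keep the disability comparison among survivors, labelled as not a randomised comparison.

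The cost is a few lines of wording. Outcomes at 9 months are known, and survival and disability at 5 years are already to be collected, so no new data are needed. The downside is that the composite mixes death with disability, which is why its components must appear alongside it.

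### The planned chi-square test ignores the order of the disability score and, if three or more levels are kept, usually loses power against a one-directional shift

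*Protocol*

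**What the plan says.** The Introduction asks as its second question: "Are there differences in neurological disability between the 2 groups at 5 years". Outcome measures lists "Neurological disability at 5 years", with no instrument, number of levels or cut-point. Statistical analysis fixes the method: "Comparison of disability scores between 2 groups by chi square test". It names no trend test, rank test or effect estimate for this outcome.

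The sample is capped by the parent trial. Methods states: "All patients who were alive at the end of the dexamethasone study (n=340) will be eligible".

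The only disability figures are binary and come from the parent trial at nine months. Severe disability was "34 of 187 patients [18.2 percent] among survivors in the dexamethasone group vs. 22 of 159 patients [13.8 percent] in the placebo group, P=0.27". Death or severe disability combined gave "odds ratio, 0.81; 95 percent confidence interval, 0.58 to 1.13; P=0.22".

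**The concern.** The word used for this outcome is scores, which points to an ordered measure. A Pearson chi-square on k levels spends k−1 degrees of freedom on any pattern of difference and carries no direction. The question has a direction: the Introduction records the worry that corticosteroids could lower case fatality yet leave more patients disabled. With three or more levels, a significant chi-square alone would not say which arm fared better.

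Power is also scarce. No more than 340 patients can be assessed, fewer once deaths before 5 years are removed, and recruitment cannot add to them. The choice of test is one of the few things still open, alongside complete follow-up and covariate adjustment.

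**Working it through.** **1. Reproducing the document's figures.** The protocol states no power, alpha or effect size for disability, so there is no planning figure to reproduce. Its parent-trial results do reproduce.

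- Survivors, severe versus not: 34/153 against 22/137. Uncorrected chi-square = 346 × (34×137 − 153×22)² / (187×159×56×290) = 346 × 1292² / 482,863,920 = 1.196, P = 0.274 (stated 0.27).
- Odds ratio among survivors = (34×137)/(153×22) = 1.38.
- Death or severe disability, taking deaths as randomised minus survivors (274−187 = 87; 271−159 = 112): (121×137)/(153×134) = 0.81, P = 0.216 (stated 0.81 and 0.22).

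Power to detect 18.2% against 13.8% with 187 and 159 patients is about 19%.

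**2. Method for an ordered score.** Assumed: two-sided 5%, independent patients, and a proportional-odds shift in which every cumulative odds is multiplied or divided by the same OR. Example: a placebo proportion of 0.50 in the best level has odds 1; dividing by 1.38 gives 0.725, a proportion of 0.42.

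- Pearson: Σ(O−E)²/E on k−1 df.
- Wilcoxon: z = [W − n₁(N+1)/2]/√V, with V = (n₁n₂/12)[N+1 − Σ(m³−m)/(N(N−1))], m being the level totals.

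The 340 survivors are split 184 to 156 in the parent trial's ratio (340×187/346 = 183.8). The placebo distributions are assumptions: (.50, .25, .15, .10) for four levels and (.40, .25, .15, .10, .10) for five.

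| Survivors, 184 v 156 | OR | Chi-square | Wilcoxon |
|---|---|---|---|
| Four levels | 1.38 | 24% | 36% |
| Five levels | 1.38 | 22% | 38% |
| Four levels | 1.7 | 55–58% | 72–76% |
| Five levels | 1.7 | 54–56% | 75–77% |

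The ranges reflect the direction of the shift; repeat simulations move the figures by about two points. Type I error was 4.7–5.3% for both tests, so the gain is not bought with false positives.

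**3. Dependence on the number of levels** (187 v 159, OR 1.38, other assumed distributions with severe disability at 13.8% on placebo).

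| Levels | Chi-square | Wilcoxon |
|---|---|---|
| 2 | 20% | 20% |
| 3 | 26% | 35% |
| 4 | 25% | 39% |
| 6 | 22% | 41% |

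**4. Non-monotone differences.** In four assumed four-level patterns that are not a consistent shift, the ranking reverses: chi-square 66%, 37%, 35% and 21% against Wilcoxon 10%, 8%, 13% and 6%.

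**5. Death as the worst level.** The parent trial gives not severe / severe / dead = 153/34/87 on dexamethasone and 137/22/112 on placebo.

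- Chi-square contributions by level: 0.72 + 2.44 + 3.42 = 6.58 on 2 df, P = 0.037.
- Tie-corrected Wilcoxon: P = 0.077.
- With these rates taken as true, power is 63% for chi-square and 42% for Wilcoxon.
- The cumulative odds ratios differ: (187×112)/(159×87) = 1.51 for being alive, but (153×134)/(137×121) = 1.24 for being alive and not severely disabled. The middle level rose from 22/271 (8.1%) to 34/274 (12.4%) as deaths fell.

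**The case against.** The strongest reply is that the protocol never says how many levels will be tested. Its only disability results are binary, and an uncorrected chi-square reproduces them. If the follow-up uses the same split, the test has 1 df, its direction is plain, and an ordinal test gains nothing. That stands, and it makes the point conditional. However, the plan speaks of scores and gives no cut-point, and collapsing the score would itself discard the ordering.

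A reader might infer that an ordinal test costs nothing. The non-monotone patterns above show otherwise, and showing the category table does not replace the lost test power.

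A reader might also infer that death should be the bottom category for all 545 patients. The documents do not support this. On the parent trial's counts the ordinal test then does worse than chi-square, and the protocol asks about mortality and disability as separate questions.

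Nor will changing the test rescue question 2: at OR 1.38 both tests have low power, and OR 1.7 appears nowhere in the protocol. Sparse cells are not shown to be a problem either, with 34 and 22 severe cases in the parent trial.

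Finally, an analysis plan may exist that defines the scale, adjustment and tables. Those details are not held against the protocol. The choice of test is different, because the protocol fixes it.

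**Conclusion.** The point holds in conditional form. Chi-square is a valid test here and no figure in the protocol is wrong; the matter is efficiency and interpretability. If three or more ordered levels are kept and the arms differ in one direction, an ordinal test among survivors gains about 12–16 percentage points at OR 1.38 (24% to 36%, 22% to 38%) and roughly 17–21 points at OR 1.7, with four or five levels. If the score is dichotomised the gain is zero; if the difference is non-monotone the gain becomes a loss.

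These sizes rest on assumed level counts, distributions and effects; only the parent trial's counts and the cap of 340 come from the protocol. The advantage persists in a smaller 5-year cohort (140 v 120, four levels, OR 1.7: 42% against 59%).

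**What to change.** In the Statistical analysis section, name the disability scale and its levels, and keep the full ordered score. Among survivors, replace the chi-square with a tie-corrected Wilcoxon rank-sum test or a proportional-odds logistic model. Report the common odds ratio with its 95% CI from the proportional-odds model, and show every category by arm. If chi-square is retained, say why; if a chi-square test for trend was meant, say so.

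Keep death out of the main disability test and read the result beside the survival analysis, since any comparison restricted to survivors depends on who survived.

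The change takes a sentence or two and standard Stata commands, with no extra data or patients. The cost is less power against non-monotone differences and a single odds ratio that assumes proportional odds. The category table lets readers judge that assumption but does not test for such a difference.

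### A chi-square test for TB relapse ignores time at risk and leaves deaths and losses before 5 years unhandled; a time-to-relapse comparison fits the question better

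*Protocol*

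**What the plan says.** The Introduction poses the third study question as "Are there differences in TB relapse rates between the 2 groups", and the Outcome measures section lists "TB relapse rate". Survival and disability are both tied to 5 years in that list; relapse is not. The Statistical analysis section then commits to "Comparison of TB relapse rate between 2 groups by chi square test". For survival the same list names "Kaplan-Meier survival estimates and log rank test".

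The population is described under Methods: "All patients who were alive at the end of the dexamethasone study (n=340) will be eligible to participate in this long-term follow-up study". On data collection, Methods says "The assessment will consist of a simple questionnaire, a clinical examination and a blood test". It also provides for a mailed questionnaire, with phone contact and local health services as back-up for those who do not reply. The section does not say which patients form the relapse denominator, how a death or loss before 5 years is treated, or whether a relapse in someone who later died is counted.

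**The concern.** The outcome is called a rate, but a chi-square test on relapsed versus not relapsed compares proportions. It has no place for how long each patient was observed. Follow-up is likely to differ between patients: some will die between nine months and 5 years, and some will not be traced. The Funding section itself treats full survival as the maximum-cost case, so later deaths are foreseen. The parent trial found a mortality difference (relative risk 0.69, 95% CI 0.52 to 0.92), and the first study question is whether it persists.

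The protocol accepts that timing and censoring matter for survival over the same years, but does not carry this over to relapse. At stake is whether a difference in relapse proportions, or its absence, reflects relapse itself or different exposure to death and loss.

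**Working it through.** The protocol gives no expected relapse rate, event count or power for relapse, so there is no design figure to reproduce. The check asks what the planned comparison would show if relapse truly occurred at the same rate in both arms.

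**Inputs**
- Window: 5 years from recruitment less the nine months of the original trial (both in the Introduction), so T = 5 − 0.75 = 4.25 years.
- Relapse risk r over the window if nobody died: assumed 3%, 5% or 10%, the same in both arms. The Introduction calls relapse data scanty and gives no figure.
- Later mortality d over the window: assumed 15% versus 15%, 20% versus 10%, and 30% versus 10%.
- Constant hazards: h = −ln(1−r)/T for relapse and m = −ln(1−d)/T for death.

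**Reading 1: patients who die without relapse count as relapse-free.** The proportion seen to relapse is

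P = h/(h+m) × [1 − exp(−(h+m)T)], where exp(−(h+m)T) = (1−r)(1−d).

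T cancels, so the window length does not affect the result. For r = 5%, hT = 0.0513:
- d = 10%: mT = 0.1054, P = 0.0513/0.1567 × (1 − 0.95×0.90) = 0.3274 × 0.145 = 4.75%
- d = 20%: mT = 0.2231, P = 0.0513/0.2744 × (1 − 0.95×0.80) = 0.1869 × 0.240 = 4.49%
- d = 30%: mT = 0.3567, P = 0.0513/0.4080 × (1 − 0.95×0.70) = 0.1257 × 0.335 = 4.21%

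| r | 20% vs 10% later mortality | ratio | 30% vs 10% later mortality | ratio |
|---|---|---|---|---|
| 3% | 2.69% vs 2.85% | 0.945 | 2.53% vs 2.85% | 0.887 |
| 5% | 4.49% vs 4.75% | 0.945 | 4.21% vs 4.75% | 0.887 |
| 10% | 8.98% vs 9.50% | 0.945 | 8.44% vs 9.50% | 0.888 |

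With 15% later mortality in both arms the ratio is 1.00. The true relapse hazard ratio is 1.00 in every row, and that is the quantity a cause-specific comparison targets.

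**Reading 2: patients who die are dropped.** If relapse carries no extra mortality, the proportion among those still alive is 1 − exp(−hT) = r in both arms, so the ratio is 1.00. If a fraction k of relapses is fatal and there are no other deaths, the proportion seen is r(1−k)/(1−rk). For r = 10% this is 0.07/0.97 = 7.2% at k = 30% and 0.05/0.95 = 5.3% at k = 50% (k is assumed). The level is understated, but equally in both arms if r and k are the same.

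**Losses.** A patient last seen relapse-free at year 2 was at risk for 2 − 0.75 = 1.25 of the 4.25 years. The chi-square test must credit either all of that window or none of it; censoring credits what was observed.

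The same test therefore estimates different things depending on a handling rule that is not stated.

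**The case against.** The strongest reply is that the 5-year horizon is implied by the study's aim, and that a simple proportion is a valid crude cumulative incidence if every patient's relapse status to 5 years is known, including those who died. That is correct. The competing-death issue is then one of interpretation. The distortion is also small beside sampling error: with the 340 patients split 184:156 (assumed, pro rata to the 187:159 nine-month survivors), power to detect a doubling of relapse from 2%, 3% or 5% is only 18%, 25% or 40%. Details of censoring are often left to a SAP. What remains is that the protocol does not leave the method open: it names a test that cannot censor.

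Four stronger readings are tempting but not supported.

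- *Fatal relapses will be missed.* A reader might infer this because the assessment described is of participating patients. But questionnaires, phone contact and tracing are also planned, the form contents are not in the text, and the protocol neither includes nor excludes relapses in patients who died. It would be an ascertainment gap, not a result of the chi-square test.
- *Dexamethasone patients will show 16% more relapses.* The ratio (187/274)/(159/271) = 0.682/0.587 = 1.16 arises only if all randomised patients are the denominator and survivors have equal relapse risk. Among survivors, the population under Methods, the same scenario gives 1.00 before later deaths.
- *Counts will be too sparse for chi-square.* The smallest expected cell is below 5 only with fewer than 11 relapses (5 × 340/156 = 10.9), and no expected rate is given. The exact size of the Pearson test at nominal 0.05 is 0.021, 0.040, 0.043 and 0.047 at 1%, 2%, 3% and 5% relapse. It is conservative, and Fisher's test is more so (0.014 to 0.036).
- *A competing-risk test such as Gray's would cure the problem.* It would not: cumulative incidence also falls where late deaths are more frequent, as the table shows. The cause-specific comparison has to lead.

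**Conclusion.** The point holds in a limited form and merits a change. The protocol fixes a test for relapse that ignores time at risk, gives relapse no horizon of its own, and leaves patients who die or are lost to be dropped or counted as relapse-free. If they are counted as relapse-free, the arm with more late deaths looks as if it relapses less, by about 5.5% (20% versus 10% later mortality) to 11% (30% versus 10%) in relative terms. This rests on assumed mortality, constant hazards and equal relapse hazards. It vanishes if later mortality is equal, and the protocol gives no basis for saying which arm, if either, would have more late deaths. A reader might infer that the relapse question will be answered wrongly. The documents do not show that; they show that the planned test cannot separate relapse from exposure to death and loss.

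**What to change.** In the Statistical analysis section, replace the chi-square test for relapse with the following.

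- Outcome: time to first relapse, up to 5 years after randomisation, censored at loss to follow-up.
- Comparison: a cause-specific log-rank test between arms, with death without relapse censored, plus a hazard ratio and 95% CI.
- Companion: 5-year cumulative incidence of relapse by arm, with death as a competing event, as description and read beside the survival results.
- Denominator: patients who survived to the end of the original trial, as under Methods, entering the risk set at that point.
- Data: for patients found to have died, record relapse status and date during the tracing already planned, and flag the source.

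The cost is a few lines of plan text, a form field and standard survival commands. Two downsides should be stated. Relapse information and dates for patients who died will be less certain. The comparison is also conditional on surviving the treatment period, which treatment itself influenced, so it should be described as a comparison among survivors and not as a fully randomised one.
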